**Figure 1 fig1:**
[figure not shown]
Overview of design and study flow.

### Participant recruitment

Potential participants may be in hospital awaiting discharge or they may already be at home following stroke. In both situations the recruitment procedure will take place over at least two occasions. Screening will take place before consent. First, potential participants will be identified by a clinician, who will check whether potential participants meet the eligibility criteria. If potential participants meet the eligibility criteria, the clinician will make the initial approach to the potential participant, and give the person an invitation letter and Patient Information Sheet (PIS) [approved by the local Research Ethics Committee (REC)]. The clinician will ask the person’s permission to pass their contact details onto a member of the research team. The participant will have at least 24–48 h to read the PIS and to discuss their participation with others outside the research team (e.g., relatives or friends) if they wish. The researcher will go through the PIS and explain the project to make sure the person understands the nature and intensity of the interventions, the randomisation procedure and a participant’s right to withdraw at any time without compromising their care and research governance issues. The researcher will answer questions, confirm the participant’s eligibility and take written informed consent if the participant decides to participate. Those who consent to participate will be assessed at baseline. Following this, participants will be randomised, and the Trial Manager will contact participants by telephone to inform them when their next assessment will be (usual care group) or organise their first therapy appointment and provide the therapist name (task-specific training group). Details of all participants approached for the trial and reason(s) for non-participation (e.g., reason for being ineligible or participant refusal) will be documented.

Strategies being employed for achieving adequate participant enrolment include (a) increasing the number of sites; (b) increased phone and email communication; (c) prompt resolving of local issues relating to recruitment challenges; (d) visiting the sites when possible, and (e) sending a newsletter with news about the trial.

### Study methods

Participants will be stratified according to severity of upper limb impairment, and state (NSW, and Victoria) using randomised permuted blocks (block sizes 4 and 6) in a 1:1 ratio. Baseline severity of upper limb impairment will be categorized using scores on the ARAT (subgroups defined by Morris et al. (43) (Group 1: score 0–3; Group 2 score 4–28; Group 3 score 29–57)). Randomisation will occur after baseline assessment using a computer-generated random allocation sequence, created by the Data Sciences unit at the HMRI. The Trial Manager will randomise each participant using REDCap, then inform the therapist of the treatment allocation and book assessment appointments.

Outcome assessors will be blinded to the treatment group to which a participant is assigned. Owing to the nature of this behavioural intervention, therapists delivering treatment cannot be blinded. Participants will be instructed in their treatment but will be blinded to the treatment group.

### Data collection

Data will be collected and stored using a web-based database REDCap, hosted by HMRI on a secure server. After giving consent, a baseline assessment will be conducted for the participant. As well as the outcome measures, demographic data will be collected at baseline including:

Whether thrombolysis or clot retrieval was used (if this information is available)National Institute of Health Stroke Scale (NIHSS)Assessment of upper limb sensory deficit including proprioception (Wrist Position Sense Test (44)) and touch (Tactile Discrimination Test (45))Ability to perform voluntary finger extension (within the Fugl-Meyer Assessment, by test item 25 -‘extend all fingers’)The Montreal Cognitive Assessment (MoCA) (46), a rapid screening instrument for mild cognitive dysfunction. It assesses different cognitive domains: attention and concentration, executive functions, memory, language, visuoconstructional skills, conceptual thinking, calculations, and orientationSelf-efficacy using the Stroke Self-Efficacy Questionnaire (47)Depression using the Hospital Anxiety and Depression Scale (HADS) (48) or the Stroke Aphasic Depression Questionnaire (SADQ) (49). To determine which of these scales is used, language is assessed using the Sheffield Screening test for Language Disorders (receptive language subsection) (50). If the participant scores less than 9 out of 9 on the receptive subsection, the SADQ is administered, instead of the HADSPresence of vascular risk factors, comorbid conditions such as cognitive decline, arthritis and renal disease, other neurological disease, and type of stroke -ischaemic/haemorrhagic, lacunar/large artery/other, cortical/subcortical, whether thrombolytic drugs were used, side of hemiplegia, handedness whether able to walk independently at stroke onset, and whether active hand movement was present at stroke onset.

Assessments will be conducted at home or in a designated clinic room in a hospital or in a research institute attached to a hospital by blinded assessors who are different to the therapists delivering treatment. Outcome assessors receive 1.5 days training with CI [name] and/or CI [name] and the local trial manager, including tutorials and practice of each assessment, and on the wider context of the trial, adhering to trial methods (e.g., avoiding being unblinded), and completing the participant case report form. This is followed by two actual participant assessments supervised by an experienced assessor.

Every effort is made to complete the follow-up assessments at 6 weeks and 6 months. In the event that the participant is unable to complete all the assessments, priority is given to at least attempting to obtain the primary outcome measure the ARAT, and then the MAL and the EQ5D-5 L, if possible.

### Modifications due to Covid-19

In March 2020, in NSW, recruitment, assessments and therapy were temporarily stopped for 4 months whilst modified procedures were developed and piloted to adjust to the presence of Covid-19 in the community. Modifications to the assessment and therapy procedures (listed below) were adopted and then recruitment was restarted at sites that were not under Covid-19 restrictions. In Victoria, restrictions were experienced from March 2020 to March 2022. In addition, state and site-specific adjustments were made. For example, in accordance with advice from NSW Health, the following will also apply to all research staff in contact with participants in this study: COVID-19 Vaccination will be mandatory for all NSW staff with first vaccination required by 30 September 2021 and second vaccination by 30 November 2021 in order to continue to work for NSW Health. Evidence of vaccination for the research staff in contact with participants will be provided. Modifications were approved by the ethics committee.

A further pause of recruitment, assessments and therapy occurred in NSW in September 2021 due to NSW Government and University of Newcastle restrictions regarding contact with participants and conducting field work. Due to the adverse effect of Covid-19 on recruitment, as well as lower than expected recruitment rates prior to the advent of Covid-19, during the data monitoring committees of 2020 and 2021, a more realistic expected number that could be recruited was proposed, which was 100 participants.

#### Changes to therapy procedures

Changes have been made to the procedures for conducting the task-specific therapy sessions, in order to adapt to the Covid-19 pandemic, as follows:

COVID19 screening questions are applied prior to the visit. If the person indicates that in the last 14 days they have been overseas, in contact with someone who has returned from overseas, in contact with any person confirmed as Covid-19 positive, in contact with someone with suspected case of Covid-19, or suffering respiratory symptoms, therapy visits are postponed until the participant’s symptoms abate and they test negative for COVIDIf there is a pause in therapy due to any of the reasons in point 1 above, the missed treatment sessions can be added after the 6-week treatment period, up to a period of 8 weeks from the first treatment sessionTherapists are required to have completed minimum level education and training in Infection Prevention and Control related to COVID-19 and provide certificate; and are requested to a have a recent influenza vaccination, and provide evidence to the trial manager if they haveAll contents of the therapy kits (including the suitcases) which cannot be cleaned effectively have been replaced with versions of the item that can be thoroughly cleanedPhysically distance as much as possible during the visit so that at least 1.5 M is between therapist and carer/participantDisposing of waste in the person’s home before leaving using the usual waste streamsTherapists have been provided with gloves, masks, disinfectant cleaning spray and alcohol/detergent wipes, and a thermometer for temperature screening. In case of a period of high community transmission of COVID19 occurring, additional PPE will be provided, including disposable gowns and eye protectionTraining sessions maybe conducted *via* video call, *via* zoom, if a participant does report as having Covid-like or respiratory symptoms, or is confirmed as having COVID-19, but feels they can still do upper limb exercises, until such time as they can be seen in person again.

#### Changes to assessment procedures

Changes have been made to the procedures for conducting the baseline measures and outcome assessments, in order to adapt to the Covid-19 pandemic, as follows:

COVID19 screening questions are applied prior to the visit. If the person indicates that in the last 14 days they have been overseas, in contact with someone who has returned from overseas, in contact with person confirmed as Covid-19 positive, in contact with someone with suspected case of Covid-19, or suffering respiratory symptoms, assessment visits are postponed until the participant’s symptoms abate and they test negative for COVIDAssessors are required to have completed minimum level education and training in Infection Prevention and Control related to COVID-19 and provide certificate; and are requested to a have a recent influenza vaccination, and provide evidence if they haveAll contents of the assessment kits (including the suitcases) which cannot be cleaned effectively have been replaced with versions of the item that can be thoroughly cleanedPhysically distance as much as possible during the visit so that at least 1.5 M is between assessor and carer/participantDisposing of waste in the person’s home before leaving using the usual waste streamsAssessors have been provided with gloves, masks, disinfectant cleaning spray and alcohol/detergent wipes, and a thermometer for temperature screening. In case of a period of high community transmission of COVID19 occurring, additional PPE has been provided, including disposable gowns and eye protectionDuring periods of high community transmission of COVID19, in order to limit exposure of participants, and assessors to infectious agents, assessment items that can be conducted by phone, are being conducted by phone. The assessments being conducted by phone are:

Modified Rankin ScaleMotor Activity LogNational Institute of Stroke Scale. Items 9 and 10Client Services receipt Inventory

8. During periods of high community transmission of COVID19, the baseline assessment has been split into 3 sections which are performed at different days/times (within 1 week of each other), in order to limit exposure of participants, researchers or staff to infectious agents.

### Data management

The end of the trial for an individual participant is defined as completion of the 6-month follow-up. The definition of the end of the trial as a whole is the date when all participants have completed their final assessment at follow-up or have been lost to follow-up.

The Trial Manager/research assistant at each site will enter data into REDCap. The Data Sciences unit at HMRI will develop and upload the randomisation schema; develop and maintain the data management system; develop a data management plan for the data; prepare and clean the data for analysis; write the statistical analysis plan and conduct the statistical analysis.

The Trial Manager/research assistant will collect information about the number of eligible participants approached, recruit the participants, including obtaining consent from those who choose to join the study and will ‘track’ each participant to ensure data collection at the designated times.

Study staff will review of data for accuracy during data entry, with data quality aided by logging of data entry and changes (with comments). The Trial Manager/research assistant will also be responsible for the secure storage of data coming from participants across research sites. Paper records of assessment scores and questionnaires will be anonymised using code identifier and kept in a locked filing cabinet in an office that is locked when not occupied by the research team.

### Sample size

We aim to detect a minimal clinically important difference of 5 points on the ARAT, which derives from findings of van der Lee et al. (51), who reported a difference of 5.7 for a mildly impaired population. The clinically important mean change for the ARAT for different severity groups are not yet published. We have adjusted to 5 to reflect the inclusion of moderate to severe impairment in our expected population, [our previous feasibility study population included 37% participants with severe (i.e., ARAT 0–3) impairment] (17). Based on observed values from our feasibility study, i.e., a pooled standard deviation on the ARAT of 18 and a correlation between baseline and follow-up of 0.72, 300 participants (150 per group) will provide the study with 80% power to detect the 5 point change on the ARAT at the 5% significance level (two-tailed test), allowing for a 20% loss to follow-up. Using similar assumptions, the study would have 80% power to detect differences between groups of 0.3 SDs on the WMFT, MAL, and the Caregiver Strain Index.

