### Protocol amendments

The protocol was updated twice following trial registration. Both updates occurred after enrolment was initiated on 12/12/2018 as outlined below.

Post-enrolment revision #1 (randomized accrual at this time = 12): The first revision was made 27/08/20.

New recruitment sites Berkley Vale Private Hospital and Mt. Wilga Private Rehabilitation Hospital were added. Outcome measures were added: the Stroke Self-Efficacy Questionnaire, Sheffield Screening Test Receptive Skills, Stroke Aphasic Depression Questionnaire and Hospital Anxiety and Depression Scale. A stretching document was produced to guide the use of stretches during the task specific visits. An ‘Upper Limb Usual Care Therapy Log’ form was developed for treatment of participants allocated to receive usual care. A column for ‘time’ was added to the Therapist’s ‘Task Specific Therapy Log’ form for each task specific exercise. Extra clarification of surrounding time between baseline and task specific therapy, with task specific therapy starting 1 week after baseline, and that participant assessments should occur within 3 days either side of an appointment which is cancelled. A document describing the assessment of fidelity to treatment intervention was developed. Adjustments to assessment and therapy procedures for Covid19 were added.

Post-enrolment revision #2 (randomized accrual at this time = 31). The second revision was made 15/09/21.

New recruitment sites, the Central Coast Local Health District and the Mid North Coast Local Health District of NSW, and Eastern Health and Western Health, in Victoria. Further advice re COVID-19 Vaccination will be mandatory for all NSW staff with first vaccination was added.

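### The sample-size section still claims 80% power with 300 participants, while the article elsewhere gives 100 as the realistic number; at 100, power for 5 ARAT points is about 37% to 43%

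*Protocol article*

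**What the plan says.** The Sample size section of the protocol article sets the target: "We aim to detect a minimal clinically important difference of 5 points on the ARAT". It bases the calculation on "a pooled standard deviation on the ARAT of 18" and "a correlation between baseline and follow-up of 0.72", with a two-sided 5% test and 20% loss to follow-up. It concludes that "300 participants (150 per group) will provide the study with 80% power to detect the 5 point change on the ARAT". For other outcomes it adds that, under similar assumptions, "the study would have 80% power to detect differences between groups of 0.3 SDs on the WMFT, MAL, and the Caregiver Strain Index".

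The section Modifications due to Covid-19 describes pauses in recruitment, and recruitment that was slower than expected even before the pandemic. It reports that during the 2020 and 2021 data monitoring committees "a more realistic expected number that could be recruited was proposed, which was 100 participants".

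The Protocol amendments section lists two revisions. The first is dated 27/08/20, with 12 randomised. The second, dated 15/09/21, begins "Post-enrolment revision #2 (randomized accrual at this time = 31". Neither entry mentions the sample size. The primary hypothesis in the abstract and in Study aims and hypotheses is still a difference of at least 5 ARAT points at 6 weeks. The Statistical analysis section specifies an analysis of covariance with baseline ARAT as covariate, fitted within a mixed model.

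**The concern.** The only power statement in the article belongs to a number that the article itself describes as unrealistic. A reader cannot tell whether 300 or 100 is the operative target. If it is 100, there is no statement of what the trial can detect or how precisely it will estimate the effect.

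The trial is presented as a Phase III test of effectiveness built around one clinically important difference. If it ends near 100 and the result is not significant, a reader who relies on the printed 80% may take that as good evidence against a 5-point benefit. At the power actually available, that inference would not be sound.

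**Working it through.** **Inputs.** From Sample size: difference 5 points, SD 18, correlation 0.72, two-sided 5%, 80% power, 20% loss. From Study methods: 1:1 allocation. From Statistical analysis: ANCOVA on baseline ARAT. From Modifications due to Covid-19: 100 participants. Normal quantiles are 1.96 and 0.8416, sum 2.80.

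**Effective SDs.**
- Change score: 18 × √(2 × (1 − 0.72)) = 13.47.
- ANCOVA residual: 18 × √(1 − 0.72²) = 12.49.

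**Step 1: the plan's own figure at 300.** After 20% loss, 120 per arm are analysed.
- Change score: SE = 13.47 × √(2/120) = 1.74; power = Φ(5/1.74 − 1.96) ≈ 82%. Required n = 2 × 2.80² × 13.47²/5² ≈ 114 per arm, 228 in total, and 228/0.8 = 285, which is close to 300.
- ANCOVA: SE = 12.49 × √(2/120) = 1.61; power ≈ 87%. Required n ≈ 98 per arm, 196 in total, and 196/0.8 = 245.

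The stated 80% at 300 is therefore approximately reproduced by the change-score formula, and it is conservative for the planned ANCOVA.

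**Step 2: the same inputs at 100.** After 20% loss, 40 per arm are analysed.

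| | ANCOVA | Change score |
|---|---|---|
| SE = SD × √(2/40) | 2.79 | 3.01 |
| Power for 5 points, normal | 43.3% | 38.2% |
| Power for 5 points, noncentral t | 42.4% | 37.5% |
| Difference detectable with 80% power, 2.80 × SE | 7.8 points | 8.4 points |
| The same divided by 18 | 0.43 SD | 0.47 SD |

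The ANCOVA 95% CI half-width is about 1.99 × 2.79 = 5.6 points (t quantile on 77 degrees of freedom).

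**Step 3: sensitivity to loss.** With no loss at all (50 per arm), power is 51-52% by ANCOVA and 45-46% by change score.

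**Step 4: what a null result would show.** With a half-width of 5.6, the upper confidence limit is the estimate plus 5.6. It reaches 5 whenever the estimate is above 5 − 5.6 = −0.6. At that precision, a non-significant result with an estimate of zero or more would leave the 5-point difference inside the interval.

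**Step 5: secondary outcomes.** At 300, the detectable effect is 2.80 × 1.61/18 = 0.25 SD (ANCOVA) or 2.80 × 1.74/18 = 0.27 SD (change score), so the stated 0.3 SD is met if the correlation is 0.72. At 100, it rises to 0.43-0.47 SD under the same assumption.

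**The case against.** The best defence is that the article is open about the shortfall. It gives the number 100, the reasons for it and the setting in which it was raised. It also says only that 100 was proposed. With no amendment logged, 300 may still be the formal target, and the power statement is then a correct description of the original design. The abstract also commits to reporting mean differences with 95% confidence intervals, which limits the harm from reading significance alone. These points stand as far as they go. They explain how the two numbers came about, but they do not tell the reader which one governs, and they supply no power or precision for 100.

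Some stronger readings are tempting and should be resisted.
- A reader might infer that 300 is a miscalculation, because the planned ANCOVA needs about 245. The change-score route gives 82% at 300, and sizing on change scores while analysing by ANCOVA is conservative rather than wrong.
- A reader might infer that the trial has been formally resized to 100. The article does not say so.
- A reader might project the accrual dates forward to show that 300 is out of reach. The slow period falls within Covid-19 restrictions and before the sites added at the second revision could contribute, so that projection is not reliable, and the point does not need it.
- A reader might suspect that the target was lowered after sight of outcome data. The Data monitoring section provides unblinded outcome data only once numbers exceed 50, and 31 had been randomised in September 2021. This makes such influence unlikely, although the article does not state that there was none.

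**Conclusion.** The inconsistency is real and should be corrected: the printed power does not describe a trial of 100. On the plan's own inputs with 20% loss, power for 5 points at 100 is 42-43% by the planned ANCOVA or 37-38% by change score. With that loss, a true 5-point benefit would be missed more often than found; with no loss, ANCOVA gives roughly an even chance. No variant comes near 80%.

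The figures assume that SD 18 and correlation 0.72 hold in this trial and that losses are equal in the two arms. The mixed model also uses the 6-month measurement, and this could shift precision at 6 weeks slightly if data are missing; the article gives no figure from which to size that. The 0.43-0.47 SD for the secondary outcomes further assumes that the ARAT correlation applies to them. The article says only that similar assumptions were used.

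**What to change.** 1. Reconcile Sample size with Modifications due to Covid-19 by stating which target is operative.
2. If it is 100, give for that number, with the formula named: power for 5 points (42-43% by ANCOVA or 37-38% by change score, with 20% loss), the difference detectable with 80% power (7.8 or 8.4 points) and the expected ANCOVA 95% CI half-width (about 5.6 points).
3. Replace the 0.3 SD statement with roughly 0.43-0.47 SD for the secondary outcomes, labelled as assuming a correlation of 0.72.
4. Keep 300 with 80% power only as the original target.
5. State that a non-significant result whose confidence interval includes 5 points does not exclude the minimal clinically important difference.
6. Add an entry to Protocol amendments with the date, the accrual at that time and the reason. If it is true, say that the change was made without unblinded outcome data.

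The cost is revised wording and one amendment entry. No extra participants or assessments are needed, and the analysis model is unchanged. The stated power becomes less favourable.
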